### Accelerometer Data Processing

Raw data will be processed in R using the most up-to-date GGIR package, a widely used open-source code [21]. This will involve a calibration to local gravity [22], adjustment for nonwear time, and a filter for abnormally high values. Nonwear time will be defined as periods of at least 60 consecutive minutes with low acceleration variability [23]. The vector magnitude of the 3 axes will be used to calculate activity-related acceleration using Euclidian Norm minus 1g [ENMO=√(x2+y2+z2)-1]. For segments with invalid data, the average of similar time-of-day data points from other days of measurement in the same individual will be imputed. Data will be included if wear time is at least 600 minutes/day on 4 or more days. Data will be used to quantify overall PA expressed as acceleration in milligravity units (mg), as well as time spent in activities at different intensities using the intensity thresholds proposed by Hildebrand et al [24]: light intensity, acceleration 30-100 mg; moderate intensity, acceleration 100-400 mg; vigorous intensity, acceleration higher than 400 mg.

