#### Primary Outcome Measure

The primary outcome measure of Active Choices is moderate intensity self-managed PA (equivalent to recommended guidelines of 150 minutes/week [12]) assessed by accelerometer devices. Accelerometers are now widely recognized as an affordable, practical, and highly accurate means of assessing PA [15]. We will use a triaxial accelerometer (wGT3X+, ActiGraph, Pensacola, FL) to assess PA using the same protocol at the 3 measurement time points. Participants will wear the device on their nondominant wrist for 7 consecutive days (24 hours) and keep a diary to record times when they attended treatment with their EP or physiotherapist, when the device was removed, and sleep hours. Upon return, the raw data from the device will be downloaded and processed. The 24-hour wear-time protocol will record raw acceleration and will be used to quantify overall time in moderate PA (inclusive of land and water-based activities), as well as time spent in light and vigorous intensity activities, sedentary behavior, and sleep. Moderate intensity self-managed PA will be calculated as the difference between total moderate intensity PA minus supervised PA performed during treatment (recorded in the diary).

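### In a 24-hour wear protocol, the 600-minute valid-day rule is not limited to waking hours, so a day with overnight wear and about 2 waking hours of wear is accepted for the primary outcome

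*Protocol article*

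**What the plan says.** Under Primary Outcome Measure, the wear instruction covers the whole day and night: "Participants will wear the device on their nondominant wrist for 7 consecutive days (24 hours". The same recording also yields sleep time. Participants also "keep a diary to record times when they attended treatment with their EP or physiotherapist, when the device was removed, and sleep hours". The outcome is built from this recording: "Moderate intensity self-managed PA will be calculated as the difference between total moderate intensity PA minus supervised PA performed during treatment".

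Under Accelerometer Data Processing, the inclusion rule is "Data will be included if wear time is at least 600 minutes/day on 4 or more days". Nonwear is identified from the signal alone: "Nonwear time will be defined as periods of at least 60 consecutive minutes with low acceleration variability". For segments with invalid data, "the average of similar time-of-day data points from other days of measurement in the same individual will be imputed". No text links the diary's sleep hours to the wear-time rule. No minimum of waking or daytime wear is set, no cap is put on the imputed share of a day, and nothing is said about hours for which no other day has data.

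**The concern.** A wear-time threshold should ensure that the hours in which the outcome can occur were mostly observed. A 10-hour threshold covers much of the waking day when devices come off at night. Here the device stays on at night, so sleep can supply most of the 600 minutes and the threshold says little about daytime wear.

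At stake is the quality of the primary outcome. A record may pass as valid while most of its waking time is imputed or missing, which adds measurement error. It could add bias if daytime wear differed between arms or between baseline and Week 24. Participants are not blinded (Study Design and Setting) and the Active Choices arm has two additional telephone consultations (Interventions), so such a difference is possible. The rule as written would not reveal it.

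**Working it through.** **The plan's own figure.** The 600-minute threshold has no derivation to reproduce. The sample size is the one derived figure tied to this outcome, and it bears on the cost of the fix. Inputs from Sample Size: difference 11 min/day, SD 12.7 min/day, power 80%, significance level 5% (taken as two-sided).

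n per group = 2 × (1.96 + 0.84)² × 12.7² / 11² ≈ 20.9, so 21 per group and 42 in total. The stated 42 is reproduced.

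**Inputs for the wear rule**
- Threshold: 600 min = 10 h per day on at least 4 days (Accelerometer Data Processing).
- Wear period: 24 h per day for 7 days (Primary Outcome Measure).
- Sleep per night, S: not given. Assumed 8 h, range 7 to 9 h.
- Assumption: the device is worn through the night and sleep is not flagged as nonwear.

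**A day that only just qualifies**
- Waking time = 24 − S
- Waking wear needed = 10 − S
- Unobserved waking time = (24 − S) − (10 − S) = 14 h, whatever S is
- Unobserved share = 14 / (24 − S)

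| Sleep (h) | Waking time (h) | Waking wear needed (h) | Unobserved waking time (h) | Share of waking day |
|---|---|---|---|---|
| 7 | 17 | 3 | 14 | 14/17 = 82.4% |
| 8 | 16 | 2 | 14 | 14/16 = 87.5% |
| 9 | 15 | 1 | 14 | 14/15 = 93.3% |

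Over the full 24 hours, 600/1440 = 41.7% is observed and 840/1440 = 58.3% may be unobserved.

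**A week that only just qualifies** (4 such days, nothing usable on the other 3)
- All hours: 4 × 10 = 40 of 168 h, or 23.8%.
- Waking hours at 8 h of sleep: 4 × 2 = 8 of 7 × 16 = 112 h, or 7.1%.
- At 7 h of sleep: 12 of 119 h, or 10.1%. At 9 h: 4 of 105 h, or 3.8%.

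**What imputation can do.** If the device was worn at the missing hours on other days, those days fill the gap. If it comes off at the same hours every day, no donor data exist and the hours stay missing. The article sets no minimum number of donor days.

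**If the 600 minutes must be waking wear.** At 8 h of sleep, 10 of 16 waking hours are observed (62.5%) against 2 of 16 (12.5%) now. With overnight wear this corresponds to 600 + 480 = 1080 min of total wear; for 7 to 9 h of sleep the range is 1020 to 1140 min.

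**Room in the sample for exclusions.** Applying the stated 20% loss and 10% device noncompliance in turn, 52 × 0.8 × 0.9 = 37.4, below the 42 required. Covering both would take 42 / (0.8 × 0.9) = 58.3, so at least 59 participants.

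**The case against.** The strongest reply is that the article does not say sleep counts. It says only wear time, and it collects sleep and removal times from which waking wear can be derived. The authors may have meant 600 waking minutes and left the detail to a fuller document. That is possible, and if so one phrase settles the point. But the article does state a threshold, and applied as worded within a 24-hour protocol that threshold admits the days described. Very still sleep might be flagged as nonwear under the 60-minute definition, but the text does not rely on this.

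A second reply is that participants are asked to wear the device throughout, so 2 waking hours will be rare, and same-person imputation will often fill gaps. This stands as a limit on the size of the problem. It does not justify the threshold, because imputation has neither a cap nor a donor minimum. The sensitivity analyses promised under Data Analyses are not specified.

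A reader might go further and infer a large error in the outcome. For example, with 10 min/day spread evenly over 16 waking hours and only 2 hours recorded, 10 × 120/960 = 1.25 min/day is captured, a shortfall of 8.75. If 10% of one arm were so affected, its mean would fall by about 0.9 min/day. The documents do not support this as an estimate. It needs every accepted day to be minimal, the same hours missing each day so that no donor exists, the gap counted as zero, and an invented 10% confined to one arm. Both arms follow the same accelerometer protocol at the same three time points, and nothing shows that daytime wear will differ.

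A reader might also infer that a stricter rule is free because 10% device noncompliance is already allowed for. The arithmetic above shows that it is not. The objection that a stricter rule removes records from an already short sample is therefore sound and must be weighed.

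**Conclusion.** The concern holds as a badly set rule. Under the stated wording, a day with overnight wear and about 2 waking hours of wear (1 to 3 hours for an assumed 9 to 7 hours of sleep) counts as valid for an outcome that occurs while awake. Fourteen waking hours of such a day may be imputed or missing. These figures are the minimum the rule permits and rest on assumed sleep duration and overnight wear; they do not describe expected compliance. The documents do not allow the size or direction of any resulting bias to be estimated, and they do not show a difference between arms. Severity is minor to moderate.

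**What to change.** Under Accelerometer Data Processing, define a valid day as one with at least 600 minutes of wear outside sleep, and keep the requirement of 4 or more such days. Take sleep from the diary, and from device-detected sleep where the diary is missing, so that inclusion does not depend on diary completion alone. Keep the all-wear 600-minute rule as a named sensitivity analysis. If 600 waking minutes was already intended, adding that phrase is enough.

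No new data are needed, and the Results section says that recruitment had not begun, so the rule can be set before any outcome data are seen. The cost is that some records with short daytime wear will be excluded from a sample that does not fully cover its own stated losses (37.4 expected against 42 needed). The number of records excluded by the rule should therefore be reported by arm and visit, alongside the result under the all-wear rule.

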### Sample Size

The reference parameters used to calculate the sample size were based on a recent large-scale survey conducted by our team, which examined accelerometer-measured PA in nearly 700 adults living in Brisbane, Australia. This study found participants accumulated an average of 10 minutes/day (70 minutes/week) of at least moderate intensity PA [11]. For our study, sample size was calculated based on change in accelerometer-measured PA, from baseline to 24 weeks, between the 2 groups, in order to detect a minimum average increase of 11 minutes/day (77 minutes/week) of moderate intensity PA. In addition to the PA observed in our reference study [11], this is equivalent to the minimum amount required to achieve standard Australian PA recommendations of 150 minutes/week of moderate intensity PA [12]. Assuming an average of 10 minutes/day (standard deviation of 12.7 minutes/day) at baseline, power of 80%, and significance level of 5%, our power analysis determined that a minimum sample size of 42 (21 in each group) is needed to detect a minimum average increase of 11 minutes/day in moderate intensity PA. To allow for 20% loss to follow-up and 10% noncompliance with PA device use, 52 participants will be recruited to the study (26 in each group).

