### Interventions

#### Active Choices Program

Participants attending EP or physiotherapy practices allocated to the Active Choices intervention group will receive a 12-week program consisting of two 1-hour face-to-face consultations (held in Weeks 1 and 12) and two 30-minute telephone consultations (held in Weeks 4 and 8), which participants will complete individually with an Active Choices consultant.

The program is based on the COM-B Framework [13] and incorporates evidence-based behavior change strategies to support participants’ transition to self-managed PA. These strategies comprise education, goal setting, goal review, self-monitoring, social support, action planning, barrier identification, and problem solving. Strategy selection was also informed by the findings of a systematic review completed by the research team, which identified those utilized in previous intervention studies associated with increased self-managed PA among military service veterans [14].

During consultations held in Weeks 1, 4, and 8, participants will create their individualized Active Choices program, with the support of a consultant, for the proceeding 4 weeks; consistent with our sample size calculations and main outcome measure, focus will be on encouraging weekly activities that elicit self-managed moderate intensity PA equivalent to the recommended guidelines of 150 minutes/week [12], although lighter and more vigorous intensity activities will also be options clients can include in their program where appropriate. This will involve identifying PA preferences and linking participants to preferred activities in their local community, setting PA goals, developing a PA action plan, identifying barriers to PA, and problem-solving solutions to overcome these. Participants will also be actively linked to other participants in their area to facilitate the formation of PA social groups. In addition to these program elements, education about PA will be delivered to participants in Week 1, and a review of previously set PA goals will be conducted in Weeks 4 and 8. At the final consultation in Week 12, participants will review their progress throughout the program and develop a plan for continuing to self-manage PA.

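### The sample size is planned on at-least-moderate activity, but the primary outcome counts only the 100-400 mg band, so permitted vigorous activity earns no credit

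*Protocol article*

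**What the plan says.** Four parts of the protocol article bear on this.

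- **Sample Size.** The reference is a survey by the same team in which "participants accumulated an average of 10 minutes/day (70 minutes/week) of at least moderate intensity PA". The target of 11 min/day (77 min/week) is explained as what must be added to that level to meet the 150 min/week recommendation. The target itself is then labelled moderate intensity.
- **Primary Outcome Measure.** "Moderate intensity self-managed PA will be calculated as the difference between total moderate intensity PA minus supervised PA performed during treatment". Vigorous time is a separate quantity: the device data also yield other measures, "as well as time spent in light and vigorous intensity activities, sedentary behavior, and sleep".
- **Accelerometer Data Processing.** The bands are "moderate intensity, acceleration 100-400 mg; vigorous intensity, acceleration higher than 400 mg". Moderate therefore has an upper limit.
- **Active Choices Program.** The focus is moderate activity, but "lighter and more vigorous intensity activities will also be options clients can include in their program where appropriate".

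Data Analyses names accelerometer-measured moderate intensity activity as the modelled outcome. No section adds vigorous time to it or defines a combined moderate-to-vigorous measure.

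**The concern.** The variable used for planning has no upper intensity limit, and the variable to be analysed stops at 400 mg. The change happens within the Sample Size paragraph: the 70 min/week is at-least-moderate activity, while the 77 min/week added to it is called moderate. The sum that justifies the target therefore combines two different quantities.

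The outcome can also score a participant contrary to the program's aim. Someone who meets the activity goal partly through more intense exercise, as the program allows, gets no credit for those minutes. If they replace moderate minutes, the score falls although activity has not. At stake are the meaning of the primary result and the match between the 11 min/day target and what is measured.

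**Working it through.** **1. The plan's own figure.** Inputs from Sample Size: difference 11 min/day, SD 12.7 min/day, power 80%, significance level 5% (two-sided assumed; sidedness is not stated). Allocation is 1:1 (Study Design and Setting). With the normal approximation:

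n per arm = 2 × (1.960 + 0.842)² × 12.7² / 11² = 2 × 7.849 × 161.29 / 121 = 20.9, so 21 per arm and 42 in total.

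This is the stated number. Power at 21 per arm is 0.801. A t-test version gives 22 per arm. The arithmetic is sound.

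**2. Where the target comes from.** 70 + 77 = 147 min/week, about 150. The 70 is at-least-moderate time, so the 147 corresponds to the guideline only if vigorous minutes count.

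**3. How the written definition scores a participant.**

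| Change in behaviour | Outcome at 100-400 mg | Outcome at or above 100 mg |
|---|---|---|
| Adds 11 min/day at 100-400 mg | +11 | +11 |
| Adds 11 min/day above 400 mg | 0 | +11 |
| Replaces 5 min/day of 100-400 mg with 5 min/day above 400 mg | -5 | 0 |

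This follows from the definitions alone. The subtraction adds a related ambiguity. Supervised activity is taken off moderate time without being limited to the moderate band, so supervised vigorous minutes could lower the outcome further.

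**4. What it could do to power.** The documents give no vigorous time and no moderate-only mean or SD, so only a range under assumptions is possible. Suppose a share v of the 11 min/day between-group gain is vigorous and so uncounted, with the SD held at 12.7:

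| v (assumed) | Counted difference | n per arm for 80% | Power at 21 per arm |
|---|---|---|---|
| 0% | 11.00 | 21 | 0.80 |
| 5% | 10.45 | 24 | 0.76 |
| 10% | 9.90 | 26 | 0.71 |
| 20% | 8.80 | 33 | 0.61 |
| 30% | 7.70 | 43 | 0.50 |

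Two other assumptions give different answers:

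- If the SD shrinks in the same proportion as the difference, n stays at 21 per arm for every v.
- If the moderate-only baseline is below 10, the gap to the same end point widens. As an illustration, a baseline of 9 gives a gap of 21 - 9 = 12 min/day, and n = 2 × 7.849 × 161.29 / 144 = 17.6, so 18 per arm at the same SD.

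The effect on the sample size is therefore undetermined in both size and direction.

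**The case against.** The strongest reply is that moderate-only was a deliberate choice. The abstract, the aims, the outcome section and the analysis section all name moderate intensity, and the program description ties its focus on moderate activity to the sample size and main outcome. Vigorous activity is only an option. On this view the one inconsistency is how the reference survey is described. That is a fair account of the intention, but it does not remove the mismatch. If moderate-only is intended, the 10 min/day and the 77-minute gap describe another variable and need re-deriving. If at-least-moderate is intended, the 400 mg cap does not belong in the primary outcome.

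A reader might go further and infer that the definition biases the comparison towards or below zero because vigorous uptake would be greater with Active Choices. The documents do not support that. Participants in the comparison program also identify preferences and make action plans, and nothing is said about vigorous uptake in either arm.

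A striking individual example should not be read as an arm-level effect either. Moving three 20-minute sessions a week from moderate to vigorous costs 60/7 = 8.6 min/day, or 78% of the target. But 60 min/week is 86% of the survey's 70 min/week average. If 5% to 15% of one arm did this and nobody in the other (assumed shares), that arm's mean would shift by 0.4 to 1.3 min/day, or 4% to 12% of the target.

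It also stands that vigorous time and overall acceleration will be derived and that sensitivity analyses are planned, so the information is kept. The article does not say that any sensitivity analysis will use at-least-moderate time.

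**Conclusion.** The mismatch is real and rests on the text alone: planning uses activity with no upper intensity limit, the primary outcome stops at 400 mg, and the program permits activity above that limit. Added vigorous time scores zero, and substituted vigorous time scores as a loss.

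The size is unknown. It may be small, because participants are aged 50 or over, come from a treatment population averaging 67.25 years, and follow a program centred on moderate activity. The power figures above depend on assumed vigorous shares and a fixed SD. The direction of any distortion between arms cannot be established, and no error in the stated 42 is shown. This is a correction worth making because it is cheap, not a flaw that invalidates the trial.

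**What to change.** Before recruitment starts (Results says it has not), define the primary outcome as self-managed time at or above 100 mg: moderate plus vigorous time, minus supervised time at or above 100 mg. This matches the at-least-moderate reference in Sample Size, so the stated calculation keeps its basis. Keep time at 100-400 mg and time above 400 mg as secondary outcomes.

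If a moderate-only outcome is intended, re-derive the reference mean, SD and target for the 100-400 mg band, and add time at or above 100 mg as a prespecified sensitivity analysis.

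The first option needs no new data, since vigorous time is already derived. It costs one processing threshold, rewording wherever the primary outcome is named, and a registry update. The second keeps the label but needs moderate-only figures from the reference survey, which the article does not report.

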### Ethics Approval

The study has received approval from The Departments of Defence and Veterans’ Affairs Human Research Ethics Committee (DDVAHREC/OUT/2019/BN11979933; December 13, 2019) and The University of Queensland Human Research Ethics Committee (#2020000034; January 31, 2020).

## Results

The study was funded by the DVA in April 2019. Liaison with EP and physiotherapy practices began in February 2020. However, the study was suspended on March 20, 2020 due to the COVID-19 pandemic and restrictions to face-to-face research activities. Our aim is to commence participant recruitment when it is feasible and safe to do so. In our project timeline, the target duration for participant recruitment is 3 months, with study implementation planned to run for 9 months. We expect that results will be available 6 months after data collection is completed.

## Discussion

The purpose of this study is to test Active Choices, a stepped-down behavioral support program to help DVA clients (ADF veterans and their dependents) self-manage PA as they transition from treatment by an EP or physiotherapist. Findings from the systematic review recently conducted by our research group suggest that such programs have the potential to promote short-term PA changes in US military service veterans with high-risk comorbidities (eg, diabetes, posttraumatic stress disorder, musculoskeletal disorders). Among those selected studies that compared a stepped-down intervention to a “usual care” group (n=14), 79% of studies (11/14) observed a positive between-group intervention effect, with the mean magnitude of change being 53 minutes/week of self-reported moderate intensity PA [14].

While this evidence is promising, our review identified no studies with ADF veterans. Similarities may well exist with US military service veterans; however, there is no direct evidence of generalizability to the Australian context or indeed outside of the United States to military service veterans in other countries. The proposed study will therefore contribute important evidence to an identified research need, and the findings provide valuable pilot data to inform larger effectiveness trials at the national level. Beyond this, our study will also address other limitations in the veteran evidence base. These include the use of self-report rather than objective measures of PA change and importantly, lack of data concerning the extent to which self-managed PA programs can benefit the psychological well-being and social connectedness of veterans or their dependents.

